**Figure 3. F3:**
[figure not shown]
Images of the outdoor space at the conventional Early Learning and Child Care programs (ie, usual care sites).

A priori power analysis was conducted using G*Power (Heinrich-Heine-Universität Düsseldorf) to estimate the sample size required to detect meaningful group differences over time for the primary objective of the study (ie, child outcomes). Given the complexity of general linear mixed-effects models and the limited availability of accessible power calculation tools for these models, a repeated-measures ANOVA with a within-between interaction was used as an approximation. This approach allows for estimating power to detect changes within participants over 3 time points and differences between 2 groups (experimental vs usual care). The calculation assumed a small effect size (*f*=0.20), a power of 0.80, and an alpha level of .05. This choice aligns with findings from systematic reviews indicating that ELCC interventions often yield small but statistically significant effects on children’s development [24]. Based on these parameters, the estimated required sample size is 42 child participants (21 per group). While our primary analyses use general linear mixed-effects models, this conservative ANOVA-based estimate provides a reasonable benchmark for planning purposes and may underestimate statistical power. Given the open cohort design, in which participants may enter and exit over time and contribute varying numbers of observations, precise specification of variance and correlation parameters is challenging at the design stage. In the absence of prior data, assumptions were therefore based on conservative estimates. To further strengthen these estimates, an internal pilot approach will be used whereby preliminary data from the first year of the study (ie, Wave 1: T0, T1, and T2) will be used to estimate key parameters (eg, variance components and within-subject correlation). These estimates will inform a refined assessment of sample size and statistical power for the remaining study period. This process will not involve formal hypothesis testing and will not affect the integrity of the primary analyses. The current sample size estimation is treated as a minimum threshold. In practice, we aim to enroll 100% of children attending the outdoor-focused ELCC center (ie, experimental site) and seek to match this number across the usual care sites. Therefore, we anticipate a substantially larger sample size that will improve the precision and generalizability of our findings [25].

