Descriptive statistics are used to summarize participant characteristics and all primary measures, including developmental assessments, movement behaviors, caregiver attitudes, support behaviors, and educator outcomes. Means and SDs are reported for continuous variables, and frequencies and percentages for categorical variables. General linear mixed-effects models will be used for the primary objective and secondary objectives 1 and 2 to examine differences in change over time and between groups. Separate models will be specified for child developmental outcomes (eg, motor, cognitive, and social-emotional), movement behaviors (eg, physical activity, sedentary time, and sleep), caregiver attitude and support measures, and educator-reported measures (eg, job satisfaction, health and well-being, and attitudes toward outdoor play). Models will include fixed effects for time (eg, T0 and T1), group (experimental vs usual care), and relevant covariates (eg, child age, sex, disability status, race and ethnicity, parent income, parent education, and newcomer status). For covariates with small subgroup sizes, distributions will be examined prior to modeling; where sparse categories are identified, categories will be collapsed as appropriate to ensure stable estimation. A random effect for participant (study ID) will be included to account for within-subject correlations across time points. The primary analyses will treat the 3 usual care sites as a single group. Sensitivity analyses will additionally adjust for the ELCC site (included as a fixed effect) to examine potential differences between individual usual care centers and to evaluate the extent to which such differences may influence the results.

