Interaction terms (eg, group × time) are tested to examine whether changes over time differ between the experimental and usual care group, thereby estimating intervention effects as differences in change from baseline. Because baseline measurements are included as part of the repeated outcome in the mixed-effects models, this approach inherently adjusts for baseline differences between groups. The mixed-effects models accommodate unbalanced data, such that participants are not required to have observations at all time points; individuals with missing baseline or follow-up measurements contribute all available data to the analysis. These missing time points are handled within the maximum likelihood framework under a missing at random assumption, avoiding listwise deletion. Missing data within completed measurement occasions (eg, partial or item-level missingness) will be explored and, where appropriate, addressed using additional methods (eg, multiple imputation) based on the nature and extent of missingness. Model assumptions are checked using residual diagnostics. Statistical significance is set at less than *P*=.05. Effect sizes are computed and interpreted using established guidelines, with CIs reported to aid interpretation of both statistical and practical significance. Interim analyses are conducted after each year of the study and final analyses will be conducted after all data collection is complete (Figure 1). All analyses are conducted in R version 4.4.2 [28] using RStudio version 2024.12.0+467 [29].

### Secondary Objective 3

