### Strengths and Limitations

This study has several notable strengths. The longitudinal cohort design enables temporal comparisons between outdoor-focused and conventional ELCC programs, providing insight into developmental changes over time. The study is appropriately powered, and the use of a naturalistic cohort design adds rigor and ecological validity. A comprehensive set of valid and reliable child outcome assessments, including both direct measures and caregiver-reported tools, ensures robust data collection. Additionally, this study examines changes in educator well-being, an area that has received little attention in outdoor-focused ELCC programs.

Despite this study’s strengths, there are limitations that we anticipate having a potential impact on the findings. Due to the naturalistic design of this study, randomization is not possible, which may influence causal inferences. Families self-enroll in the outdoor-focused program, introducing the potential for selection bias. However, both the experimental and usual care sites are funded through the Canada-wide Early Learning and Childcare program, where caregivers put their name on a city-wide waitlist and typically accept whatever program has capacity. Similarly, educators also self-select and apply to work at the center of their choice, and the outdoor-focused ELCC prioritizes educators who have training in outdoor-focused childcare, introducing a possible selection bias. To address this, we will explore baseline differences and focus our analyses on differences in change over time, inherently accounting for individual differences. Accessibility is also limited, as the outdoor-focused center is located outside the city center and is not yet reachable by public transit, potentially leading to a less diverse sample. Selection bias is likely, as families participating in the SPROUT and/or SPROUT-able studies may have an interest in child development, movement behaviors, and/or outdoor play, which could influence study outcomes. Finally, while a strength of this study is the intentional inclusion of children with disabilities, the study remains limited by a lack of valid and reliable measures of child development and health for diverse disability types.

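### The covariates as listed do not adjust the group × time estimate, and modelling change removes only constant level differences, so age-related differences in growth rate can still bias the program effect

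*Protocol article*

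**What the plan says.** The Data Analysis Plan (Primary Objective and Secondary Objectives 1 and 2) specifies general linear mixed models with a random effect for participant. On the fixed part it says: "Models will include fixed effects for time (eg, T0 and T1), group (experimental vs usual care), and relevant covariates". The examples of covariates run from child age and sex to disability, ethnicity, family socioeconomic measures and newcomer status. The intervention effect is the group × time interaction, read as a difference in change from baseline. On confounding the plan states that "this approach inherently adjusts for baseline differences between groups".

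Strengths and Limitations acknowledges that families and educators choose their center. It answers that the team will look at baseline differences and "focus our analyses on differences in change over time, inherently accounting for individual differences". No covariate × time term is named anywhere in the article. Table 2 gives Wave 1 mean ages of 28.4 (SD 12.0) months in the experimental group and 32.4 (SD 6.9) months in usual care.

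**The concern.** Group × time is estimated from change within children. A child characteristic that does not vary over follow-up, entered as a main effect, explains where a child starts and not how fast the child develops. Differencing against baseline likewise cancels only what is constant over time. If rate of gain depends on age, family circumstances or any other factor that differs between the groups, neither device removes the resulting bias.

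Between 10 and 59 months, age-dependent rates of gain are plausible for any score that is not age-normed. Without randomization, this adjustment is the primary objective's main protection against confounding. The article presents that protection as built in when, on the model described, it is not.

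**Working it through.** **1. The plan's own figure.** The sample size rests on this choice: "a repeated-measures ANOVA with a within-between interaction was used as an approximation", with f = 0.20, "a power of 0.80, and an alpha level of .05", two groups and three time points. The repeated-measures correlation ρ is not stated ("precise specification of variance and correlation parameters is challenging at the design stage"). Assume ρ = 0.5 and sphericity (ε = 1). Then λ = f²·N·m·ε/(1−ρ) = 0.04 × 42 × 3/0.5 = 10.08, with 2 and 80 degrees of freedom, and power is 0.803. N = 40 gives 0.782, so the stated 42 reproduces. Other values of ρ give N = 82 (ρ = 0), 58 (0.3), 26 (0.7) and 18 (0.8). The present point does not alter this calculation.

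**2. Algebra.** Let y(i,t) = β(t) + γ·g(i) + δ(t)·g(i) + κ·x(i) + u(i) + e(i,t), with x fixed over time. Subtracting T0 from T2 gives [β(2) − β(0)] + [δ(2) − δ(0)]·g(i) + error. Both κ·x(i) and u(i) cancel. The main effect of x therefore cannot move the group × time contrast; only an x × time term can.

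**3. Numerical check.** One complete simulated data set had 54 and 32 children, ages drawn from the Table 2 means and SDs, three visits, total SD 1, ρ = 0.5, no true group effect, and 12-month gain falling by 0.02 SD per month of older age (assumed). The T0–T2 group × time estimates were:

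- no covariate: −0.01551
- baseline age main effect: −0.01551
- linear current age: −0.01551
- baseline age × time: −0.113
- quadratic current age: −0.096

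With 13 experimental and 5 usual-care baselines deleted, as for the late entrants reported in Results, the age main effect moved the estimate in one data set from 0.237 to 0.219. Over 150 replicates per scenario the means differed by 0.002 or less.

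**4. Size of the possible bias.** Let c be the change in 12-month gain, in SD, per month of older starting age. Expected bias = c × (28.4 − 32.4) = −4.0c. No value of c is in the documents, so a range is assumed. Simulated means have a Monte Carlo SE of about 0.02.

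| c (assumed) | −4.0c | Simulated, age main effect (complete / with late entrants) | Simulated, age × time (complete / with late entrants) |
|---|---|---|---|
| 0 | 0 | −0.02 / 0.01 | −0.02 / 0.00 |
| −0.01 | 0.04 | 0.02 / 0.02 | −0.01 / −0.01 |
| −0.02 | 0.08 | 0.10 / 0.09 | 0.03 / 0.01 |
| −0.04 | 0.16 | 0.12 / 0.18 | −0.01 / 0.04 |

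For scale, f = 0.20 with a linear interaction equals a T0–T2 difference in change of 0.20 × √24 = 0.98 SD.

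**5. Is the age gap chance?** The standard error of the gap is √(12.0²/54 + 6.9²/32) = 2.0 months, so Wave 1 alone does not settle it. Part of it is structural, however. Participants and Settings licenses 49 + 39 + 31 = 119 infant-to-preschool places in usual care, of which 10 are for infants, all at one center. The experimental site runs an infant group and aims to enroll every child. By normal approximation to Table 2, 14% to 19% of experimental children (with and without truncation to 10–59 months) but about 2% of usual-care children are under 18 months.

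**6. Direction by outcome.** The peg test, timed up-and-go, grip and executive-function tasks are given only from 36 months. The same normal approximation, truncated to 36–59 months, gives mean ages of 42.9 (experimental) and 40.4 (usual care): the experimental group is older by about 2.5 months. For children starting at 30 months or more the figures are 38.7 and 36.5; at 24 months or more, 35.1 and 33.9.

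**The case against.** The strongest reply has four parts.

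- The adjustment sentence is about baseline values of the outcome, and constant level differences do cancel. A reader might infer that the sentence is simply false. The documents do not support that; it is incomplete.
- Both lists are open (each is introduced by eg), and this is a condensed article, so covariate × time terms or a nonlinear age term may sit in a fuller plan. This stands in part: the article does not rule them out or say how age is coded, and disability status, reassessed every six months, could enter as time-varying. But the stated purpose of the interaction terms is to compare change between the two groups, which describes group × time and not confounder × time. Moreover, the two statements about what the method achieves are themselves in the article.
- A reader might infer that a younger experimental group will show a false benefit on every score that is not age-normed. The documents do not support that. They give no growth rates; the bias is zero if gain does not depend on age; age-normed scores may be little affected, and the article does not say which PDMS-3 score is modelled. For the tests given from 36 months the age gap probably reverses.
- The ages come from Wave 1 of an open cohort still recruiting. True, though the shortage of infant places in usual care will persist while those licences do.

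The article is also candid that selection bias is likely and that lack of randomization limits causal inference. That candor does not make the change analysis a remedy for confounded growth.

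**Conclusion.** The point holds as a limit on what the described model can do. Time-fixed covariates entered as main effects do not adjust group × time. Including baseline in the outcome vector removes constant level differences and nothing more. Both adjustment statements are therefore too strong for a self-selected comparison.

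Group × time can be biased wherever gain depends on age. The size is about 0 to 0.16 SD for outcomes measured at all ages, assuming slopes c from 0 to −0.04 and that the Wave 1 gap persists. For those outcomes the bias favors the experimental group if gains slow with age and disfavors it if they accelerate. Size and direction for any particular outcome cannot be read from the documents. The conclusion assumes the natural reading of the Data Analysis Plan, in which covariates have no × time terms and age enters linearly. The planned sample size is not in question here.

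**What to change.** 1. Add baseline age × time, or a nonlinear current-age term, to every child-outcome model. A linear current-age term is not enough (working, step 3).
2. Add × time terms for the key listed confounders as far as the sample size allows, and name them before the final analysis.
3. Report a sensitivity analysis restricted to the shared age range, 18 months and older.
4. Reword both adjustment statements, in the Data Analysis Plan and in Strengths and Limitations, to say that constant level differences are removed and that differences in growth rate are handled only through the named × time terms.

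A propensity score × time term is optional. It is debatable if built on caregiver attitudes, which are themselves outcomes under secondary objective 2, and it would need a way to handle the 18 children without a baseline.

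The cost is small and no new data are needed. In two simulated data sets, adding age × time raised the standard error of the group × time estimate from 0.2135 to 0.2169 (1.6%) and from 0.2246 to 0.2269 (1.0%). Further × time terms would widen the intervals somewhat more.

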#### Go-Pro Data

GoPro data will be analyzed qualitatively to capture activity participation and barriers and facilitators to outdoor play and quantitatively to analyze the level of physical activity the child engages in. Our qualitative approach to analyzing the GoPro data is in line with a previous study examining outdoor play in young children using GoPro devices [58]. The GoPro’s recorded audio and video information will be transcribed by the research team and analyzed using NVivo12 software (QSR International). Using an inductive thematic analysis, this method will allow for similarities and differences throughout the data set to be highlighted and later triangulated using both audio and visual data from the GoPro video [60]. The approach to inductive thematic analysis will follow Braun and Clarke’s recommendations [61]. First, researchers will individually transcribe the videos. We will use a combination of verbatim transcription and visual transcription to capture both audio and visual information from the GoPro videos [62]. Next, the researchers will generate initial codes. To do this, transcriptions will be synced to the original media file to allow the coders to have access to the richness of the original video, along with the transcribed data. This approach is recommended when analyzing video data [62]. After the initial coding stage, researchers will combine all codes into one document and discuss themes that emerge from the coding. When reviewing the identified themes, video recordings will be used to further enhance the themes by comparing the nuances of video data to the themes found in transcripts. We will use a modified version of the Observational System for Recording Activity in Children – Developmental Delay, an observation tool validated for children with disabilities in the early years to quantify physical activity levels in the GoPro videos [63]. Using momentary time sampling, data will be coded for the first 5 seconds of every 30 seconds [15]. This will allow for a systematic observation of child activity which is more replicable across observers.

#### World Café Focus Groups and Interviews

An inductive thematic analysis will be used to identify key themes from the World Café focus groups and individual interviews [61]. The analysis will follow the 6 steps of thematic analysis described in detail above [61]. Pseudonyms will be used for all participant names in order to ensure confidentiality. Themes will be generated under three categories: (1) acceptability and feasibility of the outdoor-focused program; (2) perceived changes in children’s physical, cognitive, and social-emotional development; and (3) barriers and facilitators to supporting outdoor play for children with and those without disabilities.

## Results

Funding for the SPROUT and SPROUT-able studies was obtained in November 2022 and January 2024, respectively. Ethics approval from the Institutional Research Ethics Board was obtained in April 2024, and data collection began in July 2024, approximately 2 weeks after the experimental site opened. The study has currently completed 1 out of 3 years (waves) of data collection. A total of 110 children and their caregivers are currently enrolled; 67 are from the experimental site and 43 from the usual care sites. Sixty-two children who were enrolled at the beginning of the study (August 2024) have completed their baseline, T1, and T2 assessments (39 experimental and 23 usual care). Eighteen children who were enrolled in February 2025 (late enrollment, missing a baseline assessment) have completed their T1 and T2 assessments (13 experimental and 5 usual care). These children comprise Wave 1 of the study cohort. As of August 2025, 19 children attending the experimental site met the criteria for being in the SPROUT-able study. Of those children, 4 had a formal diagnosis of disability, 3 had caregiver-reported functional difficulties, and 12 children were receiving additional support from an inclusion support worker. At baseline, 28 educators enrolled in the study (14 experimental and 14 usual care; Wave 1). Of those educators, 6 (4 experimental and 2 usual care) left the center between T0 and T2. Figure 5 presents a breakdown of participants from Wave 1 of the study. For a complete description of the time-invariant variables of this study sample, refer to Table 2.

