### Ethical Considerations

This study has received institutional research ethics board approval (#23/108X). Caregiver-child dyads and educators consent to 1 year of the study and are encouraged to reenroll for up to 2 years as long as the child remains at the center (refer to Figure 1 for study timeline).

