### Participants and Settings

Caregiver-child dyads are eligible to participate if children are between the ages of 10‐59 months at baseline, attend a participating ELCC center for 6 or more hours per day, 3 or more days per week, and if the caregiver can read, write, and understand English and/or French. Children with and those without disabilities will be eligible to participate in this study and efforts will be made to ensure study procedures and instruments fit the needs and abilities of children with disabilities. Educators are eligible if they are currently employed at a participating ELCC center, and they can read, write, and understand English and/or French. Participants are recruited from 2 types of ELCC programs: outdoor-focused (experimental) and conventional programs (usual care). The experimental and usual care programs are both governed by the same childcare organization and are licensed under the same provincial regulations. Given this, the centers are comparable in terms of cost per day, staffing ratios, and mealtime and nap protocols. The main difference between the centers lies in how the centers deliver the early years curriculum and where programming takes place. Details of the experimental and conventional centers’ programs, including setting, curriculum, and time outside, are detailed below.

The outdoor-focused ELCC center serves as the experimental group. This center prioritizes extended outdoor play and learning, with children spending the majority of the day outside year-round, regardless of the weather. The center is situated on 500 acres of forested land that children explore daily for learning and play. This expansive natural environment features a thick canopy of tall, established trees that provide significant shade, as well as a rich and diverse landscape with largely natural, grassy ground cover. Tree species are well mixed and include native varieties such as sugar maples, oaks, and several coniferous species. The terrain is varied, with exposed roots, rocky sections, and small but steep elevation changes, alongside wetlands and visible rock deposits that contribute to the site’s natural character and afford diverse sensory and physical experiences.

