**Figure 4. F4:**
[figure not shown]
Research garden at the experimental Early Learning and Child Care program.

Caregiver questionnaires are distributed via REDCap, a secure, institutional web-based data management platform, following each assessment and are completed within 7 days of the assessment date. Each child is assigned a unique study ID and added to a password-protected master list to securely track data across all time points. During each assessment, children complete a battery of standardized assessments appropriate to their age group and ability (details provided below). Data are recorded on hard-copy data collection forms and then entered into REDCap following the assessment. One research staff member enters the data, and another verifies it for accuracy.

Educator questionnaires are distributed following the same schedule as child assessments. Educators receive a REDCap questionnaire 3 times per year and are asked to complete the questionnaire electronically within 7 days of receiving it. Educators are also invited to reenroll in the study for up to 3 years (or a maximum of 6 follow-up questionnaires).

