#### Educator Health and Well-Being

Educator health and well-being are assessed using items from the Copenhagen Psychosocial Questionnaire, third edition. The Copenhagen Psychosocial Questionnaire, third edition, is an international research instrument designed for assessing and improving psychological conditions in the workplace [52]. International results showed acceptable to good reliability (Cronbach α >0.7) [52]. For the purpose of this study, we use items from the Job Satisfaction and Health and Wellbeing Scale.

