## Discussion

### Study Significance

The SPROUT study is the first in Canada, and to our knowledge globally, to directly and longitudinally compare a licensed outdoor-focused ELCC program with conventional ELCC programs. This research addresses a significant gap in the current evidence base regarding the short- and long-term developmental and health impacts of outdoor-focused ELCC models. By using a robust and appropriately powered design, the SPROUT study provides a unique opportunity to examine whether and how outdoor-focused ELCC models influence not only child health, development, and well-being, but also caregiver beliefs and attitudes, and the well-being, job satisfaction, and continued professional development of educators.

Importantly, the SPROUT study explores how outdoor-focused programs affect educators’ knowledge and attitudes toward outdoor play. These insights may support strategies to retain and strengthen the early childhood education workforce, a major challenge and need in Canada, given the new Canada-wide Early Learning and Child Care Act, which commits to adding 250,000 new licensed ELCC spaces in Canada by March 2026 [64]. The study also examines caregiver attitudes and support behaviors toward outdoor play, offering valuable information on how these beliefs evolve over time and differ across program types. This knowledge will serve to expand on the growing body of work being done in Canada exploring caregiver and educator perspectives of outdoor play and learning and how to support change toward promoting more outdoor play opportunities for all children [11,65]. Together, this body of literature may help inform strategies to promote outdoor play in ELCC, at home, and in community spaces.

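### Educator job satisfaction and well-being are analysed as missing at random when educators leave the job, and the article describes no follow-up of those who leave

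*Protocol article*

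**What the plan says.** Secondary objective 1 compares educator job satisfaction, health and well-being, and attitudes between the two program types. For the first two, the section on educator health and well-being says "we use items from the Job Satisfaction and Health and Wellbeing Scale", from the Copenhagen questionnaire. The forms follow the child assessment schedule: T0, then 6 and 12 months.

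The Data Analysis Plan applies general linear mixed models to the primary objective and to secondary objectives 1 and 2. Participants with missing time points keep all their available data in the model, and those time points are "handled within the maximum likelihood framework under a missing at random assumption". The sensitivity analysis named for these models adjusts for site. The one under Data Collection Procedures concerns children who did not complete the standardized protocol.

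On who takes part, Participants and Settings says "Educators are eligible if they are currently employed at a participating ELCC center". Ethical Considerations says that educators consent to one year at a time. No section describes what happens to the questionnaires of an educator who leaves.

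The Results give 14 educators per group at baseline and add: "Of those educators, 6 (4 experimental and 2 usual care) left the center between T0 and T2". No reasons are stated. Departure is not among the educator outcomes in Table 1. Study Significance says of the educator findings: "These insights may support strategies to retain and strengthen the early childhood education workforce".

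**The concern.** The outcome is satisfaction with a job, and the values go missing because people leave that job. Missing at random requires that, given the scores already recorded and the covariates, departure does not depend on the unseen score. With questionnaires six months apart, dissatisfaction can build and end in resignation between two forms without being recorded. Data collection also began about two weeks after the experimental site opened, so baseline scores there describe a very new workplace and may predict later departure poorly. That last step is an inference, not something the article reports.

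If departure depends on unseen dissatisfaction, the model replaces leavers' later scores with values that are too favorable, and the error grows with the share who leave. Each group's change over time would look better than it was. The contrast between programs would shift whenever loss differs between groups, or leavers differ from stayers by different amounts. The limitations section discusses selection into the job and answers it by analysing change over time. That does not deal with selection out of the job.

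**Working it through.** **1. The article's own counts (Results).**
- Leavers: 4 + 2 = 6 of 28, or 21.4%.
- Experimental: 4/14 = 28.6%. Usual care: 2/14 = 14.3%. Difference: 14.3 percentage points.
- Fisher exact p = 0.65. Newcombe 95% CI for the difference: about -16 to 42 points.

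The counts agree with each other, and the difference is within chance. (Table 2 lists 27 educators, 13 in usual care. With 2/13 = 15.4% the difference would be 13.2 points, which changes nothing below.)

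**2. What the planned model does with a leaver.** Let p be the share of a group without a T2 score. Let δ be the amount, in SD, by which leavers' true mean T2 score lies below the value the model implies for them from their earlier scores.
- Estimated mean = (1 - p) × stayers' mean + p × implied mean for leavers.
- True mean = (1 - p) × stayers' mean + p × (implied mean - δ).
- Overstatement in that group = p × δ.

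Leavers' earlier scores are used here. Only the part of the gap that those scores do not predict enters δ.

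**3. Effect on the contrast, with the same δ in both groups.** Overstatement = (4/14 - 2/14) × δ = 0.143δ. The documents give no value for δ, so a range is assumed.

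| δ (SD) | Experimental | Usual care | Contrast overstated by |
|---|---|---|---|
| 0.25 | 0.071 | 0.036 | 0.04 |
| 0.5 | 0.143 | 0.071 | 0.07 |
| 1.0 | 0.286 | 0.143 | 0.14 |

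**4. Different δ in the two groups.** The contrast bias is (4/14)δ_E - (2/14)δ_U. It is zero when δ_U = 2δ_E and reverses when δ_U is larger than that.

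**5. Large-sample simulation.** T0 and T2 scores were normal with unit SD and no true group effect. Loss at T2 was fixed at 4/14 and 2/14, and the estimate was maximum likelihood under missing at random. The T0–T2 correlation is not given in the article and was varied.

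| Departure depends on | Correlation | Experimental | Usual care | Contrast bias (SD) |
|---|---|---|---|---|
| Nothing | 0.3 to 0.7 | about 0 | about 0 | about 0 |
| Observed T0 score | 0.3 to 0.7 | about 0 | about 0 | about 0 |
| Unseen T2 score | 0.3 | 0.321 | 0.172 | 0.15 |
| Unseen T2 score | 0.5 | 0.278 | 0.147 | 0.13 |
| Unseen T2 score | 0.7 | 0.200 | 0.103 | 0.10 |

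The planned model thus handles departure that earlier scores explain. It does not handle departure driven by the unseen score.

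**The case against.** Missing at random under maximum likelihood is a conventional main assumption, and stating it is not an error. An article may leave a sensitivity analysis for a secondary outcome to an analysis plan that is not shown here. Both points stand, so the absence of a delta-adjusted analysis is not in itself a fault. But a later analysis plan cannot recover exit responses or reasons for leaving that were never collected.

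The effect is also small against the noise. With 10 and 12 of the baseline educators remaining, the standard error of a group difference is about √(1/10 + 1/12) = 0.43 SD, taking unit SD. A bias of 0.07 to 0.14 SD is one-sixth to one-third of that. This stands too, and it limits how much weight the point carries.

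Retention is not a stated objective, and the Study Significance sentence refers to insights about educators' knowledge and attitudes, which are measured. Departures are also already counted by group in the Results. So the case is for continuing to report them beside the satisfaction results. It is not that a promised outcome is missing.

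A reader might draw three stronger conclusions that the documents do not support:
- *That these outcomes are measured only in those who stayed.* The Data Analysis Plan keeps all available data, so leavers' earlier scores remain in the likelihood.
- *That educators contribute only while employed.* This is inferred from an eligibility criterion. The stated condition on continuing, "encouraged to reenroll for up to 2 years as long as the child remains at the center", concerns the child. The Results say that six left the center, not the study. The Wave 1 flow diagram, which is not visible here, may say more.
- *That the higher loss flatters the experimental program.* The split rests on two people, no reasons are given, and the direction needs unseen dissatisfaction of similar size in both groups.

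**Conclusion.** The point holds in a limited form. Missing at random is doubtful for educators who leave, because satisfaction is both the outcome and a plausible cause of the missing values, and the article describes nothing that would let the assumption be examined. With year-1 losses and leavers 0.5 to 1 SD below what the model implies, equally in both groups, the contrast is overstated by about 0.07 to 0.14 SD toward the group losing more staff. So far that is numerically the experimental site. The size rests on an assumed δ and on the year-1 loss shares. The bias is about zero if departure follows observed scores or is unrelated to satisfaction, and it could reverse if usual-care leavers' gap is more than twice that of experimental leavers. The current data cannot tell which of these applies. The change is worth making because it is cheap and the information is lost if it is not collected when an educator leaves.

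**What to change.** For the remaining two years:

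1. Send each educator who leaves within the consented year the existing REDCap questionnaire once at exit, with one added item on the reason for leaving.
2. Report departure by program, with reasons, beside the job satisfaction and well-being results.
3. Add one delta-adjusted sensitivity analysis that lowers the model-implied later scores of leavers without an exit response by 0.5 to 1 SD. Let the shift differ between groups, since the direction depends on it.

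The cost is an existing online form sent to about 6 people a year if year-1 losses continue, one new item and one extra analysis. The downside is incomplete response from leavers and a small ethics amendment.
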